### Blended PROMPT intervention

Blended interventions represent a relatively new approach in psychological treatments, integrating the flexibility and accessibility of digital tools with the personalized care and guidance provided by face-to-face therapy. Based on the integrated blended treatment manual, where psychologists blend the digital component with their face-to-face treatment. Blended interventions allow patients to benefit from a solution that retains the advantages of online interventions - enhanced patient self-management, cost-effectiveness and efficient use of therapist time - while allowing close monitoring and guidance by therapists. The PROMPT intervention facilitates the recording and tracking of patient progress, including tasks such as monitoring daily drug use and cravings, which will be systematically incorporated into counseling sessions.

PROMPT is a web-based intervention developed by the Swiss Research Institute for Public Health and Addiction (ISGF) and the Iranian National Center for Addiction Studies (INCAS) that was designed to be delivered as a blended smartphone intervention in addition to OMT services in Iran. PROMPT consists of a dashboard, a consumption diary, a craving tracker, and 10 modules designed to improve OMT outcomes based on the principles of MI, CRA, and CBT. Participants allocated to the blended intervention condition will receive, in addition to OMT as usual, access to PROMPT. The smartphone intervention contains modules based on psychoeducation, risk-reduction counseling, self-monitoring and visual change tracker feedback, integrated CRA, MI, and CBT. A detailed overview of the included modules can be found in Table 1.

**Table 1 Tab1:** Content of the intervention

Module	Content	Therapeutic Approach	Reasoning
Module 1: Introduction	-General overview -Introduction to the diary -Introduction to the craving tracker		Gradual introduction and preparing the patient to start the therapeutic modules.
Module 2 : Motives for change	-Pros and cons of drug use, including risks of communicable disease transmission; clarification of confidence in change	Motivational interviewing techniques [32]	A targeted increase in motivation.
Module 3: Craving and lapses	-Concept of cravings -Ways to deal with cravings -Strengthening positive experiences unrelated to substance use -Introduction and planning of daily mindfulness-based meditation exercise -Relapse prevention -Dealing with lapses/relapses -Strengthening refusal skills for use in high-risk situations	CBT [33], Community Reinforcement Approach [34], including mindfulness based meditation [35]. CBT for relapse prevention [36]	Learning to understand the cravings concept and how to handle cravings. Introduction to mindfulness exercises and creation of an exercise plan. To avoid relapses resulting in cessation of the intervention or OMT. Strengthening refusal skills for use in high-risk situations.
Module 4: Triggers	-Identifying personal high-risk situations -Recognizing seemingly irrelevant, but triggering decisions.	CBT for relapse prevention [36]	Explanation of the CBT concept of risky situations and their linkages, as well as how such situations can be avoided.
Module 5: Harm reduction	- Psychoeducation on harm reduction -Overdose prevention -Reducing high-risk sexual and substance use behaviors	Harm reduction principles [37, 38]	Psychoeducative prevention of overdose and the transmission of blood-borne viruses.
Module 6: Working on needs I	-Strengthening social contacts and positive experiences unrelated to substance use -Introduction of the activation diary -Decreasing excessive ruminations -Developing healthier sleeping habits	Community Reinforcement Approach [34], behavioral activation approach [39], excessive rumination and healthier sleep exercises [40]	To increase the number of non-drug-related enhancers and, thus, prevent relapses. To improve the handling of potentially emerging, ego-threatening thoughts and sleep problems that may arise during the introduction of OMT.
Module 7: Working on needs II	-Strengthening social contacts and positive experiences unrelated to substance use (continuation) -Introduction and maintenance of activation diary -Relationships between substance use, problems, and depressive symptoms	Social problem solving Approach [41]	To promote an understanding of the potential emergence of depressive symptoms associated with the introduction of OMT and the ego-threatening thoughts and life problems that may arise.
Module 8: Address problems	-Skills to deal with solvable and unsolvable problems	Social problem solving Approach [41]	To promote an understanding of the potential emergence of depressive symptoms associated with the introduction of OMT and the ego-threatening thoughts and life problems that may arise.
Module 9: Negative thoughts	-Inner thoughts and how they influence mood and drug-taking behaviors -Common thinking errors -Challenging automatic negative thoughts	CBT approach of our previous Internet-based study [42]	CBT-based combating of negative thoughts arising from the introduction of OMT and the negative thoughts associated with it.
Module 10: Preserve sucess	-Review of the program -List of 5 personalized points to help secure achievements	Community Reinforcement Approach [34]	Appreciation of what has been achieved; repetition and consolidation of what has been learned to increase the likelihood of long-term success.

### Dashboard

The dashboard provides a convenient and easy-to-read overview of important information. Participants can view their program start date and remaining days, scheduled follow-up assessments and their completion status, and continue the intervention modules where they left off. Additionally, participants have the opportunity to input their substance use and craving (Fig. 2) in a table and see their past use visualized in a graph.

**Fig. 2 Fig2:**
[figure not shown]
Craving tracker

### Intervention modules

There are ten self-help intervention modules. They are depicted on an overview webpage linked via the main menu. The user’s progress for each module is also listed on the dashboard. The anticipated duration of the smartphone intervention is three months; during this time, all modules are discussed with the patient’s psychologist. Patients are advised to work through the modules in their presented order unless there is an urgent need for a user to skip to a specific module. The psychologists will recommend repeating the modules that are perceived as beneficial. A progress bar in the module overview shows how far a participant has progressed in each module, turning fully green once the entire module has been completed.

### Diary

The diary is a central monitoring instrument for participants. In two tables each with 7 days representing the current and the previous week, they can enter their craving frequency and intensity for opioids on a scale from 0 to 10 and whether they used opioids, methamphetamine or other substances via three yes-no-switches. This information is visualized in two graphs, a chart per day for shorter periods and a chart per week for long term progress (Figs. 3 and 4).

**Fig. 3 Fig3:**
[figure not shown]
Consumption diary

**Fig. 4 Fig4:**
[figure not shown]
Visual feedback resulting from the consumption diary

### Other elements

PROMPT includes a section with general information related to risks associated with opioid use and an introduction of OMTs as standard treatment of opioid dependence. Additionally, some modules require participants to complete exercises by selecting checkboxes or providing written responses.

### Technical specifications

PROMPT is built on the Drupal 9 content management system and uses a relational database. It will be managed by an IT developer at the institution where the principal investigator works. Access to the program is protected by encrypted and password-secured connections. Participants only have access to their own data, while the administrator has full access to all data entered by all participants. Data is entered online by the users themselves, and the system includes built-in validation to ensure accurate data, such as accepting only numbers for certain fields and requiring certain fields to be filled out.

With the assistance of the treatment center’s psychologist, participants will register for the program by choosing a unique username and a secure, personal password to safeguard against unauthorized access. Data is stored on a web space hosted by an external provider that meets Swiss IT security regulations, and employees of the web host are required to provide biometric identification to access the infrastructure. Data is extracted from the web-based database using Drupal and PHPmyAdmin and stored locally at the PI’s institution for processing and archiving. The investigator ensures that all participants’ right to privacy is upheld and that all personnel involved in the study comply with applicable privacy laws. No individual data will be published or presented at scientific meetings.

### Training of the treatment team

The therapists involved in the study are trained in OMT and have extensive experience working in certified opioid agonist treatment centers in Iran. They will be working with participants from both treatment arms of the study after receiving additional training on integrating the PROMPT treatment protocol into their routine OMT practice. To ensure fidelity to PROMPT intervention, psychologists will also participate in weekly group supervision meetings in the first months of recruitment, followed by biweekly meetings led by our research team. The objectives of supervisory meetings are threefold: to foster the advancement of psychologists’ expertise and clinical competencies in utilizing PROMPT, to guarantee consistent implementation for participants in the intervention group, and to offer the necessary support.

### Assessments

#### Primary and secondary outcomes

The primary outcomes will be the percentage of negative urine tests for illicit, non-prescribed use of opioids (opium, heroin, tramadol) between each measurement point (baseline, 1-, 2-, 3-, 6-, and 12-month follow-up) and treatment retention indicated by weekly percentage of participants who continue participation defined as receiving planned services (i.e., opioid agonist medication, physician’s visits, counselling sessions) and completing the study assessments. Secondary outcomes will be the longest period of abstinence for illicit, non-prescribed use of opioids (opium, heroin, tramadol) confirmed by urine samples; the number of self-reported other-street-drug free days over the preceding 7 days (Timeline Follow Back method) [TLFB], [21]; the number of self-reported opioid-free days over the preceding 7 days [TLFB]; the number of missed OMT appointments; screening of methamphetamine use via monthly urine tests; identification of benzodiazepine use through monthly urine screenings; detection of THC presence via monthly urine analyses; changes in communicable disease risk-taking behaviors (Blood-borne Virus Transmission Risk Assessment Questionnaire) [BBV-TRAQ], [22]; HIV test results; symptoms of stress (Perceived Stress Scale) [PSS-10], [23] and other common mental health symptoms, such as depression (Patient Health Questionnaire) [PHQ-9], [24], anxiety (Generalized Anxiety Disorder Screener) [GAD-7], [25]; PTSD (International Trauma Questionnaire for PTSD) [ITQ] [26]; adult attention-deficit/hyperactivity disorder symptoms interview [NSC-R]; alcohol use disorder symptoms (Alcohol Use Disorders Identification Test) [AUDIT] [27]; nicotine dependence (Fagerstrom Test for Nicotine Dependence) [FTND] [28], and, client satisfaction (Client Satisfaction Questionnaire [CSQ-8], [29]. Assessments will be conducted by the participating psychologists, who will assist the patients with the input of the relevant data in the web-based questionnaires.

Furthermore, any negative effects due to the smartphone intervention will be measured via the Negative Effects Questionnaire [30] at all follow-up assessments. As an indicator of treatment adherence, data will be collected on how many modules have been completed and how many OMT physicians’ visits and counseling sessions are attended by each participant. The primary and secondary outcomes and the exact time points at which each measure will be applied are presented in Table 2.

**Table 2 Tab2:** Overview of measures and their time of assessment

	Baseline	Month 1	Month 2	Month 3	Month 6	Month 12
Sociodemographic characteristics	x					
Addiction treatment history	x					
Percentage of negative urine tests (illicit, non-prescribed opioids)		xxxx	xxxx	xxxx	x	x
The longest period of abstinence from the illicit opioids		x	x	x	x	x
Number of missed OMT appointments		x	x	x	x	x
Blood-borne Virus Transmission Risk Assessment Questionnaire (BBV-TRAQ)	x			x	x	x
Number of self-reported opioid use/free days - (TLFB)	x	x	x	x	x	x
Self-reported other street-drug use/free days - (TLFB)	x	x	x	x	x	x
Perceived Stress Scale (PSS-10)	x			x	x	x
Patient Health Questionnaire for Depression (PHQ-9)	x			x	x	x
Generalized Anxiety Disorder Screener (GAD-7)	x			x	x	x
International Trauma Questionnaire for PTSD (ITQ)	x			x	x	x
Client Satisfaction Questionnaire (CSQ-8)		x	x	x	x	x
Negative Effects Questionnaire		x	x	x	x	x
Methamphetamine (MA) urine test (monthly)	x	x	x	x	x	x
Benzodiazepine urine test (monthly)	x	x	x	x	x	x
THC urine test (monthly)	x	x	x	x	x	x
HIV test result	x			x	x	x
Adult ADHD Interview (NSC-R)	x					
Alcohol Use Disorder Identification Test (AUDIT)	x			x	x	x
Fagerstrom Test for Nicotine Dependence (FTND)	x			x	x	x

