## Methods

### Study design

We will conduct a multi-center, two-arm, parallel-group randomized controlled trial (RCT) comparing an integrated community reinforcement approach- (CRA), motivational interviewing- (MI), and cognitive, behavioral treatment (CBT)-based smartphone intervention (called PROMPT for Promoting Recovery in Opioid Maintenance and Psychosocial Treatments) suitable for blended treatment in OMT with OMT as usual. Consequently, participants in the PROMT condition will receive access to the smartphone intervention in addition to OMT as usual; participants in the OMT as usual condition will receive OMT as usual but not access to PROMPT. The Ethics Committee of Tehran University of Medical Sciences (Code: IR.TUMS.MEDICINE.REC.1399.714) and the Ethics Committee of the philosophical faculty of the University of Zurich have approved the study protocol, informational letter, and informed consent process.

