### Randomization

After potential participants have provided informed consent, been deemed eligible according to inclusion and exclusion criteria, and have completed the baseline assessment, participants will be randomized by an automated computer program into either the treatment or control group in a 1:1 ratio. Completion of each follow-up assessment will result in participants being compensated with an equivalent of 5 CHF via an online voucher. Figure 1 provides an overview of the trial flow.

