### Statistical analyses

Data will be analyzed according to the intention-to-treat principle (ITT). We will examine for differences in all primary and secondary outcome variables between the two study arms at baseline and follow-up assessments using (generalized) linear mixed models. We will specifically model repeated measures nested within participants and participants nested within treatment centers by defining respective random intercepts and slopes. Study conditions and time will be modeled as fixed effects. Appropriate distributions for non-normal continuous and/or count outcomes will be specified (e.g., negative binomial, zero-inflated, Poisson). Subject to the sample’s actual gender distribution, we will investigate the intervention’s gender-specific effects by including a gender*treatment*time interaction term. If this is not possible due to inadequate sample size (i.e., the model is not identifiable), separate subgroup analyses will be run, which will allow the determination of differential treatment effects.

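### The primary outcome treatment retention also requires completed study assessments, so it mixes staying in OMT with staying in trial follow-up

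*Protocol article*

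**What the plan says.** In the protocol article, Primary and secondary outcomes, retention is the "weekly percentage of participants who continue participation defined as receiving planned services". The planned services are listed as agonist medication, physician visits and counselling, and the definition ends with "counselling sessions) and completing the study assessments". The two conditions are joined by 'and', so both must be met.

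Three other sections bear on this:

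- Dashboard: users of the app can see "scheduled follow-up assessments and their completion status". The section on the blended intervention lists the dashboard as part of PROMPT.
- Study design: "participants in the OMT as usual condition will receive OMT as usual but not access to PROMPT".
- Randomization: "Completion of each follow-up assessment will result in participants being compensated", with no difference between arms stated.

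Recruitment allows a patient to withdraw from the study at any time, losing only further compensation. The Assessments text says that Table 2 gives the time points of the primary and secondary outcomes, but Table 2 has no row for retention. No retention outcome based on services alone is described.

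**The concern.** Retention in OMT and completion of trial assessments are different things. The Abstract asks whether adding the app improves treatment retention. Under this definition, a patient who still takes the medication and attends the clinic but skips an assessment counts the same as one who has left OMT. A patient who uses the right to leave only the study is also scored as lost to treatment.

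This is an error of construct even if assessment completion is equal in the two arms. If it is unequal, there is a second problem. The intervention includes a display of the assessment schedule that controls are not described as having, so it could act on the measurement as well as on the patient. A difference in the outcome could then arise, wholly or in part, from assessment completion rather than from OMT retention. The trial is open-label for patients and psychologists in practice, and this is one of only two primary outcomes.

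**Working it through.** **Plan's own figure.** The article gives no expected retention rate and no power calculation for retention, so there is no figure for this outcome to reproduce. The overall N = 400 comes from a three-level model whose variance components are not printed. A simple two-sample formula at d = 0.35 (two-sided 5% and 80% power) gives 129 per arm, 258 in total, and 258 / 0.70 = 369 after 30% dropout. That neither confirms nor contradicts 400. Only the 200 per arm (400 at 1:1) is used below.

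**Inputs**

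- n = 200 per arm: Sample size and Randomization.
- R, true OMT retention, equal in both arms: assumed 70%, with a range of 60% to 80%. The article's 30% dropout suggests the 70% but does not establish it (see the objection).
- c, assessment completion among patients still in OMT: assumed. The article gives no completion rate, overall or by arm.
- Two-sided 5% test of two proportions at one time point: assumed, because the article states no significance level.

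**Formula.** Under the joint definition, measured retention = R × c. With equal R, the spurious difference is R × (c_PROMPT − c_control).

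**Case A: 90% against 80%**

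1. Measured retention: 0.70 × 0.90 = 0.630 and 0.70 × 0.80 = 0.560. The difference is 0.070.
2. SE = √(0.63 × 0.37 / 200 + 0.56 × 0.44 / 200) = 0.0490.
3. Expected z = 0.070 / 0.0490 = 1.43.
4. Chance of |Z| > 1.96 = 0.298, about 30%.

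**Case B: 90% against 85%**

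1. Measured retention: 0.630 and 0.70 × 0.85 = 0.595. The difference is 0.035.
2. SE = √(0.63 × 0.37 / 200 + 0.595 × 0.405 / 200) = 0.0487.
3. Expected z = 0.035 / 0.0487 = 0.72.
4. Chance of |Z| > 1.96 = 0.111, about 11%.

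**Range.** PROMPT completion is held at 95%, and each cell gives the spurious difference in percentage points and the chance of a false-positive result.

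| True retention R | Control 90% | Control 85% | Control 80% |
|---|---|---|---|
| 60% | 3.0; 9% | 6.0; 22% | 9.0; 44% |
| 70% | 3.5; 11% | 7.0; 31% | 10.5; 58% |
| 80% | 4.0; 15% | 8.0; 43% | 12.0; 75% |

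**Equal completion.** If c is the same in both arms, the spurious difference is 0 and the error rate stays at 5%. The outcome still understates OMT retention: with R = 70% and c = 85% it reads 59.5%. A true difference between arms is also multiplied by c.

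**The case against.** Several points on the other side stand.

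- **Staff-led assessment.** Assessments are conducted by the psychologists, who help patients enter the data, and the same therapists treat both arms. The voucher is not said to differ by arm. Both features would tend to narrow a gap in completion.
- **Passive display.** A reader might infer that the app prompts patients to complete questionnaires. The Dashboard section describes information that participants can view, not a reminder. The article also does not say what schedule information controls receive, so an exclusive advantage for PROMPT is inferred, not stated.
- **The 70%.** The 30% dropout belongs to a power model with six study measurements and most naturally means dropout from the study. Treating its complement as OMT retention, and then multiplying by completion, may count one loss twice.
- **The test.** The error rates come from one two-proportion comparison, not from the planned mixed model.
- **Other data.** Missed OMT appointments are a secondary outcome, and visits and sessions attended are recorded. These would help to interpret a retention result, but they do not change how the primary outcome is scored.

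Two stronger readings are also tempting. A reader might infer that the outcome cannot be scored weekly, because questionnaires fall only at months 1, 2, 3, 6 and 12. Table 2 marks four urine tests in each of months 1 to 3, most naturally about one a week, so a weekly study measure probably exists then; the difficulty applies at most after month 3. A reader might also infer that a weekly percentage cannot enter a model of "repeated measures nested within participants and participants nested within treatment centers". The percentage summarises a yes/no status per participant per week, and that status fits a generalized mixed model.

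None of this touches the definition itself, which counts a patient still in OMT as not retained when an assessment is missed.

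**Conclusion.** The concern holds for the definition. As written, treatment retention is the joint event of receiving OMT services and completing study assessments, and it does not measure retention in OMT alone. This rests on the article's wording and needs no assumption about rates.

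The possible bias between arms is plausible but unquantified. The illustrative false-positive rates of 11% and 30%, and the wider span of about 9% to 75%, depend wholly on assumed retention and completion rates and on a single-time-point test. They show that modest completion gaps would matter, not that such gaps will occur. A reader might infer that a positive retention result would reflect nothing but questionnaire completion. The documents do not support that: completing assessments alone never makes a patient retained, and such a result would need a sizeable completion gap despite staff-led collection in both arms.

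**What to change.** - Remove the assessment-completion condition from the retention definition.
- Define retention per participant from OMT service records (medication, visits and sessions), with one written rule for when a patient counts as no longer in treatment, applied identically in both arms and regardless of whether the patient remains in the study.
- Report assessment completion by arm separately, as study follow-up.
- Add a retention row with its time points to Table 2.

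A time-to-event analysis from randomization to leaving OMT, allowing for centre, is an option but not a requirement. A participant-level weekly status in the planned generalized mixed model would also serve.

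The cost is a change of outcome wording and the extraction of service dates for all 400 participants. Attendance at physician visits and counselling sessions is already to be collected per participant, so the main extra work is likely to be medication dates and the dating of attendance.
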